## Abstract

Background: Digital educational technologies in health have been an important instrument for promoting learning, self-care, self-esteem, and security regarding prevention and health promotion actions that lead to changes in behavior, mainly for non-communicable disease patients, such as type 2 Diabetes Mellitus (DM 2). Objective: This study aimed to describe a protocol for evaluating the effect of an app for cell phones and tablets on the blood glucose of older adults with DM 2. Methods: The protocol will be used to compare the effectiveness of an application for mobile devices concerning the educational booklet in reducing Glycated Hemoglobin in older adults with DM 2 in Primary Health Care. This protocol is part of a Randomized Clinical Trial project entitled Effectiveness of a Mobile Device Application on Glycated Hemoglobin in Elderly People with Type 2 Diabetes Mellitus: a Randomized Clinical Trial. Results: The protocol was structured in the following phases: (i) sample calculation, (ii) invitation to participate in the study according to the eligibility criteria; (iii) participant registration; (iv) randomization and allocation of participants into groups (double blinding); (v) application of the intervention; (vi) post-intervention procedures (post-test); (vii) data analysis. Conclusion: It is expected that encouraging studies on the impact of a mobile application will improve and enhance health education focused on self-care for older adults with DM 2, potentially influencing the local health system by reducing hospitalizations due to conditions that are sensitive to primary care, since health promotion and prevention of DM-related illnesses will be the main focus of the application and booklet developed.

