### 2.4. Blinding

As an RCT that uses two educational technologies as an intervention, participants will be blinded only regarding the research hypotheses and not regarding the two interventions used. Therefore, blinding regarding randomization, the type of educational technology, and data analysis, pre- and post-intervention, will be applied to the leading researcher and the statistician. The entire process will be conducted by a previously trained and qualified participant from the research group. Blinding will prevent the leading researcher’s biases and prevent differentiated attention to the intervention group.

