It is worth noting that both the mobile app and the educational booklet were previously validated by researchers using experts and DM 2 older adults groups [30,31].

During the execution of the clinical trial, older adults in the intervention group (IG) will receive 30–60 min of training on how to use the application, as well as having it installed on their mobile devices by the project team. They will be informed about the continuity of the application surveyed by telephone/messaging application, every fortnight, for three months (intervention time), so that possible doubts about the use of the application can be clarified.

The participants in the control group (CG) will receive an educational booklet previously developed and validated by experts, and its content will address the same themes as the application. At this meeting, the content of the booklet will be presented, in general, for 30–60 min. After the presentation, the researcher will inform the participants that they will take the booklet with them to read, for three months (intervention time), regarding self-care with DM 2.

Regarding the exercises proposed in the application, the adaptation phase will be carried out, which consists of performing the exercises that comprise the aerobic and resistance exercise protocol proposed in the application. Thus, older adults will attend the UBS for two weeks before the intervention phase, on two non-consecutive days a week.

During the 3-month intervention, the following procedures will be carried out:Month 1—resistance exercise protocol twice a week on non-consecutive days, consisting of two series for each exercise and a 30-min walk twice a week.Month 2—resistance exercise protocol twice a week on non-consecutive days, consisting of three series for each exercise and a 30-min walk three times a week.Month 3—resistance exercise protocol twice a week on non-consecutive days, consisting of five series of each exercise and a 30-min walk five times a week.

Both groups (IG and CG) will perform the exercise intervention. All patients will receive the usual treatment (routine consultations with the Unit’s professionals) provided by the BHU, according to their individual needs, which is why the educational intervention should be considered an additional service.

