### 2.8. Post-Intervention Procedures (Post-Test)

After 3 months of using the app or educational booklet and the resistance and aerobic exercise protocol, older adults who are part of the GI will answer a questionnaire based on the System Usability Scale (SUS). The SUS is a questionnaire used to evaluate the usability of systems, products, or services. Comprising 10 items, the SUS includes the following statements: 1. “I think I would like to use this system frequently”; 2. “I found the system unnecessarily complex”; 3. “I thought the system was easy to use”; 4. “I think I would need the support of a technical person to be able to use this system”; 5. “I found the various functions in this system were well integrated”; 6. “I thought there was too much inconsistency in this system”; 7. “I would imagine that most people would learn to use this system very quickly”; 8. “I found the system very cumbersome to use”; 9. “I felt very confident using the system”; and 10. “I needed to learn a lot of things before I could get going with this system”) [45].

When comparing the SUS to other instruments used to assess usability, such as the User Interaction Satisfaction Questionnaire (QUIS) and the Usability Metric for User Experience (UMUX), it is clear that the SUS stands out in terms of versatility, as it can be applied to various systems, such as websites, mobile applications, and medical systems, in addition to being simple and easy to apply. The UMUX, despite being a concise instrument like the SUS, differs in that it focuses on the user experience, while the QUIS is more complex, evaluating user interaction through 50 questions [46,47].

Both groups repeat the assessments and laboratory tests carried out in the pre-test to compare the measurements before and after the intervention between and within groups. In this way, it will be possible to evaluate the effect of using the application on older adults. After protocol implementation, both the GI and the GC will have access to the application and the printed booklet. The stages of the clinical trial protocol are described in Figure 1.

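### The abstract says double blinding, but Section 2.4 leaves participants aware of their arm and blinds only the leading researcher and the statistician, whose blinding depends on keeping the app-only usability data apart

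*Protocol article*

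**What the plan says.** The abstract sets out the phases of the protocol and describes the fourth as "randomization and allocation of participants into groups (double blinding"). It does not say who is blinded.

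Section 2.4 (Blinding) gives the detail. On participants it says: "participants will be blinded only regarding the research hypotheses and not regarding the two interventions used". Blinding to the randomization, the type of educational technology and the data analysis "will be applied to the leading researcher and the statistician". It then adds: "The entire process will be conducted by a previously trained and qualified participant from the research group". That person is not named among the blinded roles. Among the benefits expected of blinding is that it will "prevent differentiated attention to the intervention group".

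Section 2.8 (Post-Test) says that "older adults who are part of the GI will answer a questionnaire based on the System Usability Scale (SUS"), while both groups repeat the pre-test assessments and laboratory tests. Section 2.9 (Data Analysis) describes one SPSS database and, in the same section, the scoring of the SUS. It does not say whether the SUS scores are stored in that database.

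Section 2.6 names the reduction in glycated hemoglobin as the primary outcome. The primary hypothesis at the end of the Introduction adds knowledge, self-care and self-efficacy.

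**The concern.** Readers normally take double blinding to mean that participants, and usually those who treat or assess them, do not know the allocation. A person given either a phone app or a printed booklet knows which one it is, and Section 2.4 says so. Many readers, and those who grade evidence from abstracts, would credit the trial with a protection it does not have.

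Two things are at stake. The first is how far the questionnaire outcomes can be trusted, since participants who know they received the newer technology may answer with that in mind. The second is the blinding that the plan does promise, that of the statistician. A variable collected in one arm only can reveal the coding of the arms.

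**Working it through.** No arithmetic applies, so the check is to set the sections side by side, role by role.

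1. **Participants.** Abstract: double blinding. Section 2.4: blinded to the hypotheses, not to the interventions. These do not agree under the usual meaning of the term.

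2. **Staff in contact with participants.** Section 2.4 gives the whole process to a trained member of the group and does not list that member as blinded. Section 2.7 has participants in the app group "having it installed on their mobile devices by the project team". Whoever installs the app, trains the user or presents the booklet must know the arm. No section assigns outcome assessment to a blinded person, and none assigns it to the person who delivers the intervention.

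3. **Leading researcher and statistician.** Section 2.4 states that both are blinded. These are the only two roles to which the word double could refer, and the abstract does not define it that way.

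4. **Whether the statistician's blinding can hold.** Section 2.8 has both groups repeat the same assessments, and the SUS is the only instrument described as given to one arm. Suppose the arms are coded A and B and the SUS scores are in the same file. Every SUS value then falls under one code, so a single non-missing value is enough to identify the app arm, and through the code every participant's allocation. If the SUS scores are in a separate file that the statistician does not see, nothing is revealed. Section 2.9 mentions one database and does not say which arrangement applies.

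5. **Which outcomes are exposed.** The primary hypothesis names four outcomes. HbA1c is a laboratory value, so a participant's or interviewer's knowledge of the arm has little influence on its measurement. The other three are questionnaires (Section 2.5) answered by participants who know their arm. That is three of the four outcomes in the hypothesis, but not the one that Section 2.6 names as primary.

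6. **The stated benefit.** Section 2.4 expects blinding to prevent extra attention to the intervention group. Section 2.7 describes follow-up of the app group by telephone or messaging "every fortnight, for three months (intervention time), so that possible doubts about the use of the application can be clarified", with no matching support described for the booklet group. Blinding the leading researcher and the statistician cannot remove contact that belongs to the intervention as described. This supports a more exact account of what the blinding achieves. The mismatch in steps 1 to 3 does not depend on it.

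**The case against.** The strongest reply is that Section 2.4 is the governing text and is candid. It says that participants know their intervention and it names the two blinded roles, so the fault is one parenthesis in the abstract, where double may have meant those two roles. This stands in part: nothing is concealed. It does not make the label right, because the abstract leaves the term undefined and is often read alone.

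Three stronger readings are tempting, and the document does not support them.

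- *The person who delivers the intervention also collects the post-test questionnaires.* A reader might infer this from the sentence that gives one member the entire process. But Sections 2.5 and 2.8 name no assessor, Section 2.3 has the research group's team conduct the trial, and Section 2.7 mentions both the project team and the researcher. The scope of that sentence is unclear, and an article may leave assessor assignment to the full protocol.
- *The statistician will be unblinded.* This follows only if the SUS data reach the statistician with the analysis file before the HbA1c analysis is final. A statistical analysis plan or data-management plan that is not shown may prevent it.
- *The primary result is biased.* The named primary outcome is a laboratory measurement. Nor does the document describe the knowledge scale as self-rated, so it should not be assumed to be as exposed as self-care and self-efficacy.

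**Conclusion.** The point holds in a limited form. The abstract's label contradicts Section 2.4 and should be corrected. The trial is open to participants and, necessarily, to those who deliver the interventions; only the leading researcher and the statistician are stated to be blinded. The statistician's blinding is conditional on the app-only SUS data being kept out of the analysis file until the HbA1c analysis is final, and the article does not say that they will be.

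The effect on results cannot be quantified from the document. HbA1c is largely protected at measurement, and the three questionnaire outcomes in the primary hypothesis are more exposed because participants know their arm. The conclusion rests on the usual meaning of double blinding and, for the SUS part only, on the assumption that the scores are stored in the single database. The correction is worth making before enrolment. The Final Considerations state that the protocol has not yet been implemented and that adaptations can occur.

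**What to change.** 1. In the abstract, replace double blinding with: open to participants and intervention staff; leading researcher and statistician blinded. In Section 2.4, state which steps the trained group member carries out.

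2. Hold the SUS data in a separate file, and give the statistician arms coded A/B without the SUS until the HbA1c analysis is final.

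3. Where the existing team allows, have the post-test questionnaires given by a member who did no training and no follow-up calls, with the SUS given last. The leading researcher should not take this task: questioning participants who know their arm would expose the leading researcher to the allocation and undo the blinding that Section 2.4 provides.

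The cost is a less favourable label and minor reassignment of data handling and tasks. No new data are needed. The third step depends on staffing, which the article does not describe; if it cannot be met, the report should say who gave the questionnaires and whether that person knew the arm.

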## 1. Introduction

Currently, a change in fertility and mortality rates has been emerging from the increase in longevity expectations and the number of older adults around the world.

The aging of the world’s population is happening at an accelerated pace, and as a result, global life expectancy has increased significantly. In 2020, there were approximately 1 billion people aged 60 or over, with this number expected to rise to 1.4 billion by 2030 and to reach 2.1 billion by 2050. In 1990, the average life expectancy was 64 years, but by 2019, it had risen to 73 years. In this sense, coordinated and rapid actions are essential to support healthy aging, especially in low- and middle-income countries, since 80% of the world’s elderly population will be concentrated there by 2050 [1,2].

In Brazil, older adults represented over 14% of the total population at the end of the last decade, and it is estimated that in 2050, it will increase by about 50% [3,4,5,6]. The aging process generally comprises complex changes linked to the individual’s biological, psychological, and social components, which gradually interfere with behavior and social interactions. People in the aging process sometimes re-signify goals and activities, optimizing and prioritizing their existing capabilities through new practices and technologies to remedy the loss of some skills and find other ways to perform tasks. Reframing and adapting to maintain autonomy in priority tasks are part of healthy aging, as shown in the World Report on Aging and Health [1,2].

In 2015, the 193 Member States of the United Nations (UN) came together, aiming to put the world on a sustainable path. Then, the 2030 Agenda was established to implement the Sustainable Development Goals (SDG). Health and well-being are the central points of the 3rd SDG, which aims to guarantee universal and quality access for all ages. Among the goals of the 3rd SDG is the reduction, by one-third, of premature mortality from non-communicable diseases, such as chronic non-communicable diseases (NCDs), through prevention and treatment, achieving universal coverage, and through access to essential quality healthcare services [7,8].

The 2030 Agenda highlights that the dissemination of information and communication technologies (ICT) and global interconnectivity have a great ability to accelerate human progress, eliminate digital exclusion and develop the spread of knowledge, health education and health care to the largest number of people, especially those who are out of reach of or inaccessible to traditional care [6,7,8].

It is recognized worldwide that ICT point to new opportunities for the strategic and innovative use of cutting-edge digital information. Professional training and education for the general population are essential to ensure that an additional 1 billion people benefit from universal health coverage and well-being, including during global health emergencies [9].

In this context, eHealth, which concerns the safe, economic, ethical, equitable, and sustainable use of ICT in support of health—such as in health services, health surveillance, health literacy and education, and knowledge—is of fundamental importance to achieving the goals of the 3rd MDG [9].

eHealth is included in the Digital Health strategy, which encompasses the use of other digital technologies for health, such as the Internet of Things, artificial intelligence, big data, and robotics. These digital technologies enable data storage and tools that support remote data capture and exchange, as well as information sharing. This sharing can create a chain of care with proven potential to improve health outcomes, including diagnosis, treatment, digital therapeutics, clinical trials, self-management of care, and person-centered care [9,10].

To strengthen the digital health strategy, the WHO entered into a partnership with the International Telecommunications Union (ITU) through the “Be He@lthy, Be Mobile” initiative, supporting the expansion of mobile health technology (mHealth) in health systems services to help face NCDs and support healthy aging. mHealth is defined as medical and public health practice supported by mobile devices, such as cell phones, patient monitoring devices, personal digital assistants and other wireless devices [9,10]. From mHealth, mHealth for aging (or mAgeing) emerged as a new program whose central objective is to help older adults, in the case of Brazil, people over 60 years of age, to maintain functional capacity and live as independently and healthily as possible through evidence-based self-management and self-care interventions, complementing routine care already implemented by healthcare teams [9,10].

The findings of the 10th edition of the International Diabetes Federation (IDF) showed that DM is one of the fastest-growing global health emergencies of the 21st century [9]. In 2021, around 537 million people had this condition, with projections that this number will reach 643 million by 2030, and 783 million by 2045. According to the IDF, in 2021, altered fasting glucose levels worldwide were increasingly present with advancing age in adults, reaching a peak of 8.4% in people aged 60–64. Regarding the prevalence of diabetes in people aged 65–79 in Brazil, a prevalence of 19.9% was identified, and in those over 75 years old, it was 21.1% [11].

Among DM individuals, 50 to 80% have a deficit related to knowledge about the disease and self-care skills necessary for treatment to be effective and disease prevention to be achieved. This data corroborates the results found in a study by Borba et al. (2019) that out of the 202 elderly participants, 77.7% had insufficient knowledge about DM and, regarding attitude, 85.6% had a negative psychological adjustment concerning diabetes [12]. In this sense, empowerment favors the glycemic control process, which results from autonomy and co-responsibility for treatment [13,14].

An Australian study that aimed to identify what would be a “perfect application” for DM showed that the practical aspects of self-management of the disease, the guidelines regarding the measures to be taken, reminders and alarms, as well as the approach to topics for managing stress and negative emotions were the main topics lacking guidance in an application [15].

A study by Kebede and Pischke [16] aimed to identify popular diabetes apps with functions that encourage self-management, such as monitoring blood glucose, physical activity and meal planning, and investigating the association of the use of these types of apps and other factors with cumulative self-care behavior. The study included 1682 participants (1052 with type 1 DM (DM 1) and 632 with type 2 (DM 2), of which more than half, 549 (52.2%), and one third, 210 (33.3%), of the respondents with DM 1 and DM 2, respectively, reported using diabetes self-management apps. Although participants with DM 1 reported using self-management apps more than those with DM 2, there was a greater increase in the cumulative score for self-care in participants with DM 2. It is worth noting that the number of people with DM 2over 60 years of age was three times higher than with DM 1 in the same age group, which explains the greater use of applications by people with DM 1, who are, for the most part, younger and more familiar with digital technologies [16].

Another study, conducted by Gerber et al. (2024) [17], developed and evaluated the feasibility of an eHealth diabetes prevention program adapted for older adults through a randomized clinical trial. The results showed that appropriate weight loss goals, flexible dietary composition, and accessible interventions for learning through online classrooms and fitness monitoring technology were effective in reducing weight in older adults. Participants in the intervention group had an average weight loss change of 9.5% compared to the control group, which gained 2.4% of their body weight. In this context, it was possible to observe that eHealth and mHealth interventions, which were previously considered inaccessible and ineffective for older adults, are new accessible treatment alternatives that promote active and healthy aging [17].

Corroborating the aforementioned study, in 2020, Whitehouse investigated the feasibility of diabetes self-management education and support (DSMES) via telehealth for DM 2 older adults after hospital discharge. The study showed that, 30 days after post-discharge follow-up, through interventions via a tablet with remote online meetings, participants who completed the intervention increased their diabetes knowledge scores, in addition to a 1.1% decrease in glycated hemoglobin values. Additionally, it was found that there were no hospital readmissions for any patient during the intervention period, which generated satisfaction among participants, who described the program as useful [18].

In this sense, for the DM older adult population to have a healthy aging process, they must be increasingly welcomed and included in the contemporary technological revolution. To this end, digital educational technologies in health have been an important instrument that aims to promote learning, self-care, self-esteem, and security regarding prevention and health promotion actions that lead to changes in behavior [19,20,21,22].

However, for older people to be welcomed into this technological revolution, usability must be one of the main properties of software. According to the Brazilian Association of Technical Standards (ABNT), in the International Organization for Standardization (ISO)/International Electrotechnical Commission (ISO/IEC 25010:2011), usability is defined as “the ability of the software product to be understood, learned, operated and attractive to the user, when used under specified conditions”. In this sense, applications with high usability are more intuitive, which leads to greater user satisfaction and, consequently, greater interaction with the interfaces offered and retention of the educational content of the application [23].

In a systematic review published in 2023, which aimed to develop a set of guidelines aimed at optimizing the design and usability of mobile applications for older adults, twenty-seven guidelines were identified, of which two stood out in 15 of the 40 studies included in the review, namely: simplifying the design due to the possible cognitive changes present in this population and increasing the size and distance between interactive controls, such as buttons and form inputs, to avoid accidental touches on icons [24].

Still regarding the guidelines, the others were organized into five categories, such as: “Help and Training”, which are focused on creating tutorials on how to navigate the application; “Navigation”, which should have as a characteristic the reduction in the number of alternative paths to perform a task, focusing on the current action; “Visual Design”, such as reducing the number of elements and options available on the screen and making them familiar to the elderly person, with a strong contrast between the color of the text and the color of the background, as well as the use of large fonts; Adequate “Cognitive Load” through the use of simple, short, and unambiguous language, according to the context in which the person is inserted, and finally, “Interaction”, advocating less use of the keyboard and reduced sensitivity to touch [24].

A usability study sought to identify barriers and facilitators, based on design, for completing health surveys on a mobile application among older adults participating in the Framingham Heart Study and a diverse hospital environment. Corroborating the guidelines previously mentioned, the research participants verbalized a preference for large font sizes and friendlier colors. Regarding cognitive load, older adults had no difficulty with the questions presented in the application, unless they presented long instructions. In this sense, the application was characterized by the majority as “easy and fun” and that through it they were able to understand the importance of using it to raise awareness about their own health. As a suggestion, the participants reported the importance of using voice instructions and animated tutorials [24,25].

Other studies report that older people are more likely to adopt mobile device applications when they perceive them as useful for their own health and when they feel empowered to use them through training and tutorials, which leads to greater engagement in the use of technology and a lower error rate during navigation [26,27,28].

Usability is even more important when a new digital technological tool is developed for people over 60 years old due to the digital literacy barriers they face, such as cognitive decline, decreased visual acuity and lack of familiarity with digital interfaces. Therefore, application design must incorporate usability principles, such as larger fonts that make text readable, simplified navigation, large icons, color contrast, and audio features to make technology more accessible [29].

Therefore, this study aimed to describe a protocol for evaluating the effect of an app for cell phones and tablets on the blood glucose of older adults with DM 2. The protocol aims to compare the effectiveness of an application for mobile devices concerning the educational booklet in reducing Glycated Hemoglobin in older adults with DM 2 in Primary Health Care (PHC).

The primary hypothesis of the study in which this protocol will be applied is that older adults with DM 2 who use the mobile application will have a greater reduction in glycated hemoglobin, and will have a higher level of knowledge, self-care and self-efficacy compared to older adults who use the educational booklet.

